## Abstract

**Background:**

Non-Communicable Diseases (NCDs) are rapidly increasing globally, including Pakistan. Female school teachers form a vital yet often ignored population sub-group in terms of NCDs prevalence and risk factor clustering. Despite growing burden of lifestyle associated NCDs, there is limited data on workplace based lifestyle interventions, particularly in school settings.

**Objective:**

The proposed study aims to evaluate the effectiveness of a lifestyle intervention on NCDs risk factors and their awareness in female secondary school teachers, as well as to identify the barriers and facilitators to its adoption.

**Methods:**

A quasi-experimental mixed methods study will be conducted in public secondary schools of Islamabad city, Pakistan, including both an intervention and control group. The study will be divided into three phases; baseline assessment, intervention development and implementation, and an end-line assessment. Comparisons will be made between control group and intervention groups, as well as pre and post intervention. Following the end-line assessment, in-depth interviews will be conducted on a sample of teachers to explore the barriers and facilitators to adoption of lifestyle changes. A total of 130 teachers, recruited through purposive sampling, will be divided into 2 groups of 65 in intervention and control groups each. The intervention will span 9 months, and consist of bi-weekly education and training sessions on lifestyle modifications. The sessions will include topics relevant to nutrition and physical activity, and take home resources such as sample menus, list of healthy food options etc. Primary outcomes of the study include anthropometric measurements including weight, body mass index (BMI), waist and hip circumference (WHC), waist to hip ratio (WHR). Secondary outcomes will include knowledge and awareness of NCDs and their associated risk factors.

**Discussion:**

The study aims to reduce NCDs risk factors among female teachers by incorporating tailored lifestyle interventions including both nutrition and physical activity. This study intervention can help promote overall health of working females, improve workplace wellness and foster a culture of health promotion and disease prevention in educational settings. The findings will facilitate policy-makers to generate sustainable health strategies to empower teachers to take control of their health, and build a healthier educational workforce.

## Introduction

1

Non-communicable diseases (NCDs) are rapidly increasing in prevalence globally, and account for 74% annual deaths worldwide (1). Diabetes, hypertension, and cardiovascular diseases are among the top most prevalent NCDs, with diabetes effecting 529 million people around the world (2). Hypertension currently impacts 626 million women and 652 men (3), while cardiovascular diseases cases around the world have risen to 523 million (4). The South-Asian region, like the rest of the world, is also heavily burdened with NCDs, where these diseases cause approximately 9 million annual deaths (5). Pakistan is experiencing growing NCD related morbidity and mortality rates, and 58% of annual deaths can be attributed to these diseases (6). Over the years, research has evidenced that majority of these NCDs emerge from an array of risk factors, both modifiable and non-modifiable. The modifiable factors include, unhealthy diet, sedentary lifestyle, tobacco use, and alcohol consumption, whereas age, gender, genetics, ethnic group are classified as non-modifiable (7). Gender plays a crucial role in NCD prevalence and associated complications. Women are more prone to developing NCDs due to increased clustering of risk factors in this gender group (8). It has been reported that 11.4% women experience a clustering of both types of risk factors. Additionally, women are more prone to remain un-diagnosed, resulting in increased complications and adverse effects (9). Women in low and middle income countries have NCD prevalence rates of 82%. Additionally, NCD associated maternal deaths reached a prevalence of 44% (10). Pakistani women report an increasing prevalence of NCD risk factors (12.5%), and diabetes (9.1%) (11).

Women in the workforce, despite working in the same environment as their male counterparts, have a heightened risk of developing non-communicable diseases due to their biological differences. Additionally, carrying both workplace and traditional domestic responsibilities puts a toll on women’s psychological health which further aggravates various pathways that lead to development of metabolic irregularities, as suggested by a systematic review conducted by Idris et al. (12). This is why employed females report 1.05 times higher risk of having multi-morbidity as compared to unemployed females (13). Work related stress has been reported to elevate the chances of developing type 2 diabetes in women as much as 12%. Increased stress levels contribute to higher cortisol levels, leading to insulin resistance, raised blood glucose levels, and higher visceral obesity, all of which contribute to diabetes mellitus and other NCDs. Additionally, increased working hours are associated with a greater risk of developing lifestyle risk factors, such as poor diet, physical inactivity, smoking and alcohol consumption, all of which further amplify chronic diseases probability (14).

Recently, a large body of evidence has depicted positive results of lifestyle modification on reducing non-communicable diseases risk factors in both men and women. Physical activity and improved diet have a significant impact on reducing weight, decreasing overall fat intake and increased fiber intake, all of which help reduce lifestyle risk factors (15). Pairing preventive cardiovascular disease screening with lifestyle interventions focused on dietary and physical activity modifications produced small but long-term health benefits in women, especially those with preeclampsia (16). Whether diet or physical activity or both produce the greatest impact on reducing non-communicable disease risk factors depends on a number of factors such as the type of diet, intensity and duration of physical activity and other physiological conditions such as pregnancy, post-partum or lactation (17). Lifestyle interventions including both nutrition and physical activity components can produce modest health impacts in as little as 6 weeks. Improvements were seen in the body mass index (BMI), arm, chest, waist and hip circumferences, body far percentage, and blood glucose levels after a one and a half month aerobic training and nutrition education community program targeted toward women aged 50 years and above (18).

Teachers working at primary and secondary schools depict similar lifestyle behaviors and have below par health status. About 80.9% of female school teachers lacked adequate nutrition knowledge, and 17.6% were obese (19). Evidence has shown that improving the lifestyle related knowledge and behaviors in teachers can directly and positively impact the nutritional and physical activity associated behaviors in students (20). Additionally, studies have found teachers to have a higher prevalence of unhealthy lifestyles and overall a poorer health status, as compared to medical professionals or entrepreneurs (21). Furthermore, poor health in teachers then leads to increased absenteeism and even early retirement as the quality of life further deteriorates. Evidence has depicted a positive impact of physical activity interventions on reducing stress, and employee turnover, while improving health outcomes. This ultimately increases the overall education system productivity and reduces healthcare costs (22).

A study carried out on Nigerian female teachers reported a significant decrease in the prevalence of hypertension, diabetes mellitus, and hypercholesterolemia following a 3 month intervention that included scheduled exercise sessions and dietary control recommendations (23). An Indian study conducted in teachers found significant increases in exercise, fruits and vegetable consumption, with a simultaneous reduction of sodium, fat, red meat and processed food intake, following a lifestyle education intervention (24). Evidence suggests that female teachers have a considerable level of unhealthy dietary patterns and these are significant implications of their nutritional habits on the dietary choices and behaviors of their students (25). Hence, promoting healthy food intakes among teachers through different interventions can not only improve their own health outcomes but also positively influence their student’s lifestyle perceptions and habits.

There is a large body of work that demonstrates the impact lifestyle interventions have on reducing the risk factors of various NCDs, however, limited data is available on the participant’s perceived barriers and facilitators to adopting a healthier lifestyle, as evidenced by a systematic review on the subject (26). A meta-analysis of qualitative studies explored the supporting and constraining factors toward the adoption of lifestyle interventions in pre-diabetics. One of the key highlighted theme was the internal struggle of making these changes, which participants reported to be overwhelming and daunting to incorporate in their daily life (27). Another study implemented lifestyle interventions at the workplace and reported their positive impact which led to a significant decrease in health related stress, thereby also improving work performance (28). A study, focused on increasing lifestyle intervention adoption in obese women, reported key findings to tailor a behavior change program; incorporating holistic health model in education sessions, administer personalized feedback and individualized goal setting to remove barriers, and focus on building sustainable lifestyle changes that can be continued even after the program ends (29). Sustainability of lifestyle changes can be ensured when participants receive adequate support from their healthcare team as well as their social circle including close family and friends. Group settings provide a high degree of relatedness with others as well as feeling supported by a community to make changes in lifestyle. Constant participant feedback in the form of in-depth interviews or focus group discussions provide insight into their perceived barriers and facilitators in the process, and can form the basis of developing successful lifestyle interventions (30).

There is a major research gap in Pakistan regarding the NCD epidemic among women. In recent years Pakistan has managed to contribute only 1.7% to the global female NCDs bibliometric analysis. A lack of evidence based research which can be further translated into policies and programs to overcome the NCD epidemic is majorly missing in Pakistan’s response to NCD prevention and control. Working females particularly teachers have an even greater risk of NCDs as they are consistently exposed to stressful situations and a lack of time, both of which have established associations with the occurrence of non-communicable disease risk factors. Targeting a lifestyle intervention to this population group can help promote a healthier lifestyle in female educators, which is also seen to indirectly improve the health behaviors of their pupils, by acting as role models. Improved health status of teachers is also linked with improved productivity and reduced health costs. This study can help prioritize, develop and implement women specific recommendations to reduce NCD prevalence in this gender group.

Hence, the overall aim of this study is reducing the non-communicable disease (NCDs) risk factors and improving knowledge and practices regarding NCDs and their risk factors among female public secondary school teachers in Islamabad. The specific objectives are:

To carry out baseline assessment of NCDs risk factors in female public secondary school teachers in Islamabad.To determine baseline knowledge, attitudes and practices regarding NCDs and their risk factors in female public secondary school teachers in Islamabad.To adopt and implement a lifestyle (nutrition and physical activity) intervention to reduce the burden of non-communicable disease risk factors and improve their associated knowledge, and practices in female public secondary school teachers in Islamabad.To carry out an end line assessment to determine the feasibility of up-scaling the intervention and explore the barriers and facilitators toward its adoption in female teachers of public secondary schools.

## Methods and analysis

2

### Study design

2.1

The study will be a mixed methods research, employing both quantitative and qualitative aspects in data collection and analysis. The reason for using a mixed methods study is because quantitative and qualitative researches are concerned with different questions and research paradigms. While quantitative research focuses on numbers and proportions, qualitative research delves deeper into the how’s and why’s of a research problem. Quantitative research is influenced by ‘positivism’, assuming that any problem can be measured and quantified, irrespective of its nature and underlying causes. Whereas, qualitative research employs interpretivism, which assumes that each individual has a different world view and that everyone experiences a reality in a different way. Therefore, mixed methods studies are imperative in bringing together multiple ways of looking at a research question and providing a deeper insight into the severity, underlying causes, and potential solutions to these problems (31). Furthermore, when talking about lifestyle interventions or lifestyle change programs, there remains insufficient data on the facilitators and barriers to adopting the lifestyle modification guidelines. This can be addressed by employing a mixed-methods approach incorporating strategies to identify the causes of participant engagement and adherence to lifestyle interventions, and then coming up with solutions to improve these aspects (32). Our mixed methods study can help bridge this gap in literature and provide important information needed to increase the success rate of lifestyle interventions.

Additionally, the study will be a quasi-experimental study design, specifically the difference-in-differences (DID) quasi experiment, with one intervention and one control group. The DID analysis helps to determine the impact of the intervention by measuring the change in the outcome variable over time and doing a comparative analysis between the intervention and control groups. It helps evaluate the existence and strength of a causal relationship, especially in situations when a randomized controlled trial cannot be implemented, either due to ethical reasons or lack of resources to carry out these trials. For the DID design to accurately determine the causal relationships, it assumes that both the control and intervention groups adhere to ‘parallel trends’ to each other if the intervention did not exist (33). Difference in difference studies are used frequently to assess the intervention impact in a population group, therefore it aligns with our study’s objectives. In these studies we compare the difference in outcomes between the intervention and control groups, which depicts the factors that change overtime within these groups. We analyze two differences in these experiments; the first difference is the before and after comparison in the intervention group, which tells us what factors remain the same over time despite the implemented intervention. The second difference is between the control and intervention group, which tells us what factors were influenced or changed by the intervention over time.

Our study will include a baseline assessment of all study variables, in both intervention and control group, to address the parallel trends assumptions of the DID study design. This will help establish baseline equivalence across both groups on all variables prior to intervention implementation. Although, the study only has one pre-intervention time point, this baseline similarity will strengthen the plausibility of parallel trends. Furthermore, any observable differences will be statistically adjusted for through regression modeling. This will help control any potential confounding factors in the study. For substantial baseline imbalance across key covariates, propensity score weighting will be applied within the DID framework to enhance internal validity. This approach is widely used in DID quasi experimental design studies where multiple pre-intervention points or randomization is not feasible (34).

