#### Phase 3: end-line assessment of outcome variables

2.2.3

Evaluation phase to assess the impact of the intervention in each group as well as to compare the impacts of the interventions with each other. This phase will also include in-depth interviews of participants to identify the facilitators and barriers that played a role in either helping them follow the dietary guidelines given or not be able to do so. Additionally, the reasons behind their knowledge, attitudes and practices regarding NCDs and their risk factors will be explored via focus group discussions.

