#### Descriptive statistics

2.14.1

Data will be analyzed using frequencies, percentages to report the prevalence and proportion of NCD risk factors and their associated knowledge and attitudes in the study population. A comparative analysis will be done between the baseline and end line data to study the influence of our study’s intervention in reducing the NCD risk factors and improving the knowledge and practices regarding them and their contributing behaviors.

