#### Inferential statistics

2.14.2

Paired samples t-test will be used to compare the pre and post intervention values of continuous variablesMcNemar test will be used to compare the pre and post intervention values of categorical variablesChi-square test will be applied to determine associations between different variablesRegression analysis will be conducted to estimate the direction and strengths of relationships between independent and dependent variablesTo adjust for potential confounders such as socio-demographic variables, multivariable regression models will be employed. Variables such as age, household income, education level, will be included as covariates in the DiD analysis. This will help adjust for baseline differences between control and intervention groups, ensuring more accurate attribution of the intervention’s effects. This further enhances the internal validity of the study via limiting confounding bias.To control the risk of type I error, statistical corrections will be applied for multiple comparisons, where appropriate. This will include Bonferroni correction and/or false discovery rate (FDR) correction.

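### The protocol names a difference-in-differences design but misstates how to read it, so a before-after change or a raw group difference could be reported as the intervention's effect

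*Protocol article*

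**What the plan says.** Section 2.1 (Study design) calls the study "specifically the difference-in-differences (DID) quasi experiment, with one intervention and one control group". It explains, correctly, that DiD measures change in the outcome over time and compares that change between the groups. It also states the parallel-trends assumption, and it plans regression adjustment and, for substantial baseline imbalance, propensity score weighting within the DiD framework.

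The same section then interprets two differences separately:
- "the first difference is the before and after comparison in the intervention group, which tells us what factors remain the same over time"
- "The second difference is between the control and intervention group, which tells us what factors were influenced or changed by the intervention over time"

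Other places bear on the same point:
- Abstract, Methods: "Comparisons will be made between control group and intervention groups, as well as pre and post intervention". The two kinds of comparison are not ranked.
- Section 2.2.3 (Phase 3): the evaluation is "to assess the impact of the intervention in each group as well as to compare the impacts of the interventions with each other". Section 2.2.2 gives the control group no sessions or materials until the study has ended, and there is only one intervention.
- Section 2.14.1 (Descriptive statistics): "A comparative analysis will be done between the baseline and end line data to study the influence of our study’s intervention".
- Section 2.14.2 (Inferential statistics): the paired t-test and McNemar test are listed for pre/post values, then chi-square and regression. Socio-demographic variables "will be included as covariates in the DiD analysis", and Bonferroni and/or false discovery rate correction is foreseen where appropriate.

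**The concern.** In a two-group, two-time-point DiD, the effect is one number: the change in the intervention arm minus the change in the control arm. Section 2.1 never says that one difference is subtracted from the other. It gives each difference a meaning that it does not have.

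A before-after change in the intervention arm does not show what stays the same. It is the intervention's effect plus anything that moves everyone over the nine months. A difference between the groups, taken alone, does not show what the intervention changed. It also carries whatever separated the groups at baseline.

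Both problems are live in this study. Section 2.7.1 selects schools purposively, and section 2.1 anticipates baseline imbalance large enough to need weighting. Section 2.14.1 assigns the intervention's influence to the baseline versus end-line comparison, and section 2.14.2 supplies tests for it. An analyst who follows these sentences literally could report a secular change, or a pre-existing difference between schools, as an effect when the DiD shows none.

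**Working it through.** **1. The plan's own figure.** Section 2.8 gives SD 0.96, difference 0.5, two-sided alpha 0.05, power 80% and 10% non-response.

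n = 2 × 0.96² × (1.960 + 0.842)² / 0.5² = 57.87, so 58 per group. Then 58 / 0.9 = 64.4, so 65. The stated 65 per group is reproduced, and 58 analysed per arm is used below.

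**2. What each contrast estimates.** Let the true effect be E, the drift common to both arms D, and the baseline gap (intervention minus control) G.

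| Contrast | Expected value |
|---|---|
| Before-after, intervention arm | E + D |
| Raw group difference at end-line | E + G |
| DiD (difference of changes) | E |

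Only the DiD is free of both D and G, given parallel trends. Each of the other two is exposed to one of them: before-after to drift, the raw group difference to the baseline gap.

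**3. Point arithmetic with assumed BMI means.**
- Both arms fall from 27.0 to 26.5: before-after −0.5, DiD 0.
- Intervention stays at 26.5, control stays at 27.0: group difference −0.5, DiD 0.
- Intervention 28.0 to 27.5, control 27.0 to 27.0: end-line group difference +0.5, DiD −0.5. The two contrasts have opposite signs.

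**4. Size for the before-after test, which the plan does list.** The assumptions, none of them in the document, are: E = 0, D = 0.25, 0.96 is the SD of BMI level at each time, pre/post correlation ρ, and teachers independent.

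SD of change = 0.96 × √(2(1 − ρ)); SE = SD of change / √58.

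- ρ = 0.5: SD of change 0.96, SE 0.126, 0.25 / 0.126 = 1.98. The paired t-test rejects about 50% of the time.
- ρ = 0.8: SD of change 0.607, SE 0.080, 0.25 / 0.080 = 3.14. It rejects about 87%.
- The DiD test on change scores rejects about 5% in both cases (simulation, 10,000 trials per setting: 5.3% and 4.9%).

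**5. Sensitivity to the SD.** Section 2.8 does not say whether 0.96 is the SD of a level or of a change. At ρ = 0.5 the SD of change equals the level SD, so reading 0.96 as the SD of change leaves the 50% unaltered. If the level SD were 4 (assumed), SE at ρ = 0.5 is 4 / √58 = 0.525 and 0.25 / 0.525 = 0.48, so rejection is about 8%. At ρ = 0.8, SE is 4 × √0.4 / √58 = 0.332 and 0.25 / 0.332 = 0.75, so rejection is about 11%. The bias of 0.25 is the same throughout; only the chance of calling it significant changes.

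**The case against.** The strongest reply is that DiD is plainly the intended causal design. It is named, one sentence describes it correctly, and parallel trends, weighting and covariate adjustment all attach to it and to no other contrast. That stands. A reader might infer that the protocol leaves open which contrast decides effectiveness. The text does not support so strong a claim. Moreover, the quantitative analysis figure (Figure 4) is not shown, and formal naming of the estimand coefficient may properly sit in an analysis plan.

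Several further replies also have force:
- The reference to change over time in the sentence on the second difference permits a charitable reading as a difference in changes. The sentence itself, however, describes a group difference and credits it to the intervention.
- Section 2.14.1 is headed as descriptive. It nevertheless uses the comparison to study the intervention's influence, and section 2.14.2 attaches significance tests to it.
- No end-line two-sample t-test is listed. False-positive rates for such a test would therefore not be properties of this plan, and none are claimed.
- A reader might add up the error of testing several contrasts. The plan nowhere defines success as any one of them, and section 2.14.2 foresees multiplicity correction. That correction deals with the number of tests; it does not remove bias from drift or a baseline gap.

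Regression adjustment and weighting do not rescue the before-after reading either, because a within-arm paired test makes no use of the control group.

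**Conclusion.** The point holds as an error in what the protocol states, not as a missing detail. DiD is the named design, but section 2.1 misreads its two components, section 2.14.1 takes the intervention's influence from the before-after comparison, and section 2.2.3 speaks of an impact in each group and of several interventions when controls receive none. Followed literally, common drift or a baseline gap between schools could be reported as an effect while the DiD is null.

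The figure of about 50% against 5% is an illustration. It rests on a drift of 0.25, a correlation of 0.5, SD 0.96 and independent teachers. It rises to about 87% at correlation 0.8 and falls to about 8% (correlation 0.5) or 11% (correlation 0.8) if the level SD is 4. School clustering is ignored; it would alter the rejection rates but not the bias in the contrasts. The correction should be made, because the text as it stands licenses effect claims that the design cannot support.

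**What to change.** - In sections 2.1 and 2.14.2, state that the intervention effect on each outcome is the group-by-time (DiD) coefficient, that is, intervention-arm change minus control-arm change, and that the effectiveness conclusion rests on it.
- In section 2.1, replace the two sentences that interpret the first and second differences separately with one saying that the control-arm change is subtracted from the intervention-arm change.
- Reword section 2.2.3 as a comparison of the change from baseline to end-line between the intervention and control groups.
- In sections 2.14.1 and 2.14.2, label within-arm paired t and McNemar results, and any raw group difference, as descriptive, with no claim of effect. Align the abstract.

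The cost is wording only, with no new data and no change in sample size. The one thing given up is that a significant within-arm change can no longer be offered as evidence that the intervention worked.
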